### Participant timeline {13}

Fig. 1 shows the participant timeline.

**Fig. 1 Fig1:**
[figure not shown]
Participant timeline. ICF, informed consent form; NicAlert, nicotine saliva test

### Sample size {14}

Based on a previous Cochrane review with meta-analysis [7], it is assumed that preoperative smoking cessation decreases the binary outcome of postoperative complications (yes or no) with a relative risk of 0.42. The mean postoperative CCI as a continuous measure in a retrospective chart review in a cohort without smoking cessation at the hospital of Lucerne was 13 and we therefore assume a CCI of 5.5 in the intervention group. The assumed standard deviation for the sample size calculation was 20. With anticipated 80% power, a two-sided significance level α of 5%, a sample size of 226 patients is planned. With an additional 10% dropout, our aim is to enrol 251 patients.

### Recruitment {15}

All patients scheduled for an intermediate or high-risk procedure (Additional file 2) at the hospital of Lucerne will be identified by the study nurse either through the tumour board lists or as soon as they are scheduled for surgery in the electronic health record program. Otherwise, clinicians can contact the study nurse to enrol patients who have been referred but not yet scheduled for surgery or presented at the multidisciplinary tumour board. To avoid an overload of the consulting capacities in the intervention arm recruitment of new trial participants may be paused.

## Assignment of interventions: allocation

### Sequence generation {16a}

Patients will be randomised in a 1:1 ratio to either the intervention or control group using the service of the University of Graz (www.randomizer.at). Before randomisation patients will be pre-stratified for age (≤60, >60 years) and procedure (intermediate versus high-risk procedures). Both factors have been identified in a previous retrospective cohort study at our institution as risk factors for complications. Minimization, as an efficient way to control for confounding in small to moderately sized trials, will be used. Also, minimization automatically ensures the concealment of random allocation since there is no pre-existing randomization list.

### Concealment mechanism {16b}

Minimization ensures concealment of random allocation since there is no pre-existing randomization list.

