### Trial design {8}

This investigation is a monocentric, randomized, single-blinded, controlled superiority trial involving patients undergoing intermediate and high-risk surgery [10] at the Hospital of Lucerne. Patients will be randomised in a 1:1 ratio to either the intervention or control group. Before randomisation patients will be pre-stratified for age (≤60, >60 years) and procedure (intermediate versus high-risk procedures). Minimization, as an efficient way to control for confounding in small to moderately sized trials, will be used. Also, minimization automatically ensures the concealment of random allocation since there is no pre-existing randomization list.

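### The article rests allocation concealment on the absence of a list, but minimisation on two visible factors leaves the next allocation partly to largely predictable

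*Protocol article*

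**What the plan says.** Trial design {8} asserts that "minimization automatically ensures the concealment of random allocation since there is no pre-existing randomization list". Sequence generation {16a} repeats this, and Concealment mechanism {16b} consists of that claim alone: "Minimization ensures concealment of random allocation since there is no pre-existing randomization list".

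The procedure is described in two places. Sequence generation {16a} names 1:1 allocation through an outside university's web service, with minimisation. It also says "Before randomisation patients will be pre-stratified for age" and procedure risk. Implementation {16c} says that the two factors are entered in a browser once a patient has been recruited, and that the allocation comes back at once. No probability for the minimising arm is given, and a random element is neither stated nor excluded.

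Other sections set the conditions:

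- Trial design {8}: a single centre.
- The comparator and intervention sections ({6b}, {11a}): advice only against specialist counselling with nicotine replacement. Who will be blinded {17a} describes blinding only for assessment of the primary outcome.
- Informed consent {26a}, Recruitment {15} and Participant retention {18b}: the study nurse identifies candidates, explains the study and follows up all patients.
- Recruitment {15}: "To avoid an overload of the consulting capacities in the intervention arm recruitment of new trial participants may be paused".

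**The concern.** Concealment means that whoever decides whether and when to enrol a patient cannot foresee that patient's assignment. A list is only one way in which foreknowledge arises. Minimisation creates another: the rule is a function of past allocations and the incoming patient's factors. The article presents this known weakness of the method as its safeguard. That is a wrongly stated property, not a detail left to a fuller document.

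The setting makes prediction feasible. One team can see the whole sequence, the arms are recognisable, and age group and procedure risk are known before consent. A pause triggered by intervention-arm load implies that someone watches that load.

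If the order or timing of enrolment can follow prognosis or motivation to quit, the arms may differ in ways that age group and procedure risk do not capture. Adjusting the primary model for those two factors would not remove that.

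**Working it through.** **The plan's own figure.** The article gives no figure for predictability. The trial size used below comes from Sample size {14}, whose inputs are a mean CCI of 13 for controls against 5.5 under the intervention, an SD of 20, a two-sided 5% level and 80% power. It arrives at 226 patients, or 251 once 10% dropout is allowed for.

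- Difference: 13 − 5.5 = 7.5.
- Normal approximation: n per arm = 2(1.960 + 0.842)² × 20² / 7.5² = 2 × 7.85 × 400 / 56.25 ≈ 111.6, so 112 per arm and 224 in total.
- The t-test version gives 225.2 in total, so 113 per arm and 226.
- Dropout: 226 / 0.9 = 251.1, stated as 251.

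The sample size reproduces and this point does not affect it.

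**Inputs for predictability.** From the article: 251 patients, 1:1 allocation, two binary factors. Assumed, because the article does not give them:

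- probability *p* of following the minimising arm: 1.0, 0.9, 0.8 or 0.7;
- factor prevalences: 50/50%, 60/30% and 70/20% (results hardly change);
- ties broken 50:50;
- a guesser who knows all past allocations and the new patient's two factors, and names the minimising arm.

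Each setting was simulated 400 times.

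**Formula.** If *d* is the share of allocations at which one arm is preferred, the share guessed correctly is *d* × *p* + (1 − *d*) × 0.5. When *p* = 1, *d* is the share that is fully forced.

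| Balance | *p* | *d* | Correct guesses |
|---|---|---|---|
| Marginal | 1.0 | 0.724 | 0.724 + 0.276 × 0.5 = 0.862 |
| Marginal | 0.9 | 0.759 | 0.683 + 0.121 = 0.804 |
| Marginal | 0.8 | 0.802 | 0.642 + 0.099 = 0.741 |
| Marginal | 0.7 | 0.851 | 0.596 + 0.075 = 0.670 |
| Within four strata | 1.0 | 0.496 | 0.496 + 0.252 = 0.748 |
| Within four strata | 0.9 | 0.551 | 0.496 + 0.225 = 0.720 |
| Within four strata | 0.8 | 0.617 | 0.494 + 0.192 = 0.685 |
| Within four strata | 0.7 | 0.700 | 0.490 + 0.150 = 0.640 |

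The rows are for 50/50% prevalences. With a sum-of-ranges imbalance measure, the marginal results are 86%, 80%, 72% and 65%. The deterministic within-stratum figure can be checked by hand: the scheme acts as blocks of two, so the first of each pair is guessed at 50% and the second at 100%, a mean of 75%.

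**Less informed guessers.** Someone who knows only the overall arm totals is right 71%, 68%, 64% and 60% of the time for *p* = 1.0, 0.9, 0.8 and 0.7 under marginal minimisation. Someone who always names the arm opposite to the last allocation is right about 66–68% of the time at *p* = 1.0 and 53–54% at *p* = 0.7.

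**The case against.** A reader might infer that the scheme has no random element and that 86% is therefore the trial's predictability. The documents do not support this. The article speaks of random allocation by an outside service and is silent on the probability. It is a condensed account, and the value may have been withheld so that recruiters do not know it. The omission itself is no finding, and 86% is only the upper end of a range. The figures also assume complete running tallies; the described roles make this plausible, but no section says that the study nurse keeps or sees them.

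A reader might also infer that the nurse can halt recruitment at will, even between consent and allocation. Recruitment {15} names no one and concerns new participants.

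Nor is concealment absent. Allocation by an external web service, released after recruitment, is genuine procedural protection. It does not stop a prediction made before a patient is approached, and {16b} does not rely on it.

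Two further objections stand. Restricted randomisation in general exceeds 50% for a guesser who knows the past, so 50% is not a fair target. And no bias in CCI points has been estimated: age group and procedure risk are balanced and adjusted for, and the Charlson index and ASA class are recorded at baseline. Harm is a risk here, not a demonstrated effect.

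The within-stratum reading is the less likely one, because the statistical methods section {20a} calls age and procedure risk the minimisation variables. The wording leaves it open all the same.

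None of this makes the stated reason for concealment correct.

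**Conclusion.** The concern holds in limited form. The claim that minimisation ensures concealment because there is no list is wrong in all three places where it appears. Staff with full knowledge of past allocations and the two factors could predict the next one partly to largely: 64–86% correct over all settings tried. The top figure needs deterministic marginal minimisation, and a random element of 0.7–0.9 brings it to about 64–80%. These figures rest on assumed settings and a fully informed guesser. The documents establish neither a deterministic scheme nor actual misuse. The correction is worth making because the statement is false under every setting tried and the remedy is cheap.

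**What to change.** 1. Replace the concealment sentence in Trial design {8}, Sequence generation {16a} and Concealment mechanism {16b}. Rest it on the central web allocation already planned, released only after eligibility and signed consent have been irrevocably recorded.
2. Use, or confirm, minimisation with a random element, for example a probability of 0.7–0.8 for the minimising arm, not disclosed to recruiting staff.
3. Keep running allocation tallies from recruiting staff where feasible.
4. State that any capacity pause applies before patients are approached, never between consent and allocation.
5. Say whether balance is sought on the factor margins or within the four age-by-procedure strata.

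The cost is a setting in the web service and some wording, with slightly looser balance on two factors that the primary model already includes. Predictability falls but does not vanish. At 0.7–0.8 a fully informed guesser is still right about 65–74% of the time under marginal minimisation and 64–68% within strata, so steps 1 and 3 are needed alongside step 2.

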### Implementation {16c}

Upon recruitment of a new patient, the information on the two strata will be entered through a web browser, and the new treatment allocation is provided instantaneously.

## Assignment of interventions: Blinding

### Who will be blinded {17a}

Deidentified reports will be used for the assessment of the primary outcome of perioperative complications.

### Procedure for unblinding if needed {17b}

Unblinding for the primary outcome will not be necessary.

## Data collection and management

### Plans for assessment and collection of outcomes {18a}

Throughout the study, data is documented and collected in the electronic patient chart called LUKiS, a local installation of the CMR-System by the US-based Healthcare IT-System provider Epic. Next to the clinical part, the CMR system has a dedicated research-focused module (Epic Research) to aid researchers and their associated staff in facilitating research projects by providing tailored security, population selection, patient recruitment, data collection etc.

### Plans to promote participant retention and complete follow-up {18b}

The study nurse will follow up on all patients and collect postoperative patient-reported outcomes whenever possible.

### Data management {19}

Throughout the study, patient data is collected in LUKiS in an uncoded manner; study participants will be informed accordingly. At the end of the study, the LUKiS reporting team will generate a report, which will include all study data in a de-identified form. This means that participants cannot be identified in the report by name, initials, or birth date. An identification number (code), generated by LUKiS, will be used instead. The report and the list with the identification numbers will be provided to the study team. Both the dedicated LUKiS team as well as the study team have access to the report as well as to the list with the identification numbers. Both departments store the list with the identification numbers independently from the report.

### Confidentiality {27}

The analysis of the report with the pseudonymized data will be performed by the project statistician. None other than the study staff will have access to the de-identified report. The investigator and all study staff will maintain all study documents in strict confidence.

### Plans for collection, laboratory evaluation and storage of biological specimens for genetic or molecular analysis in this trial/future use {33}

Nicotine abstinence will be confirmed by using the NicAlert saliva test. The test will be performed by an advanced nurse practitioner during a routine hospital visit of the participant. The NicAlert saliva test is a point of contact test detecting six ranges of cotinine concentrations from 0 to 2000+ ng/ml. The only data collected is the category of concentration. No biological samples will be stored, and no further laboratory tests will be carried out. The test kit and the saliva sample will be immediately destroyed after use.

## Statistical methods

### Statistical methods for primary and secondary outcomes {20a}

A detailed statistical analysis plan has been written up as an Additional file 3 to the submission. According to the intention to treat (ITT) principle, patients will be analysed according to the treatment group they have been assigned to by randomisation. The full analysis set (FAS) consists of the patients randomized and receiving surgery within 4 months after randomization. The FAS will be the primary population for the efficacy analysis.

Primary outcome CCI will be addressed with a multiple linear model, including a randomized treatment group, and the minimization variables (age ≤60 or >60 and intermediate or high-risk surgery) as independent variables. If after normality check with a qq-plot the residual distribution is skewed a transformation of the CCI may become necessary. To evaluate the between-group difference in CCI of the smoking cessation intervention versus the control group, adjusted for the above-defined confounders, the estimated between-group difference with 95% confidence interval and corresponding p-value will be reported. For the secondary outcomes, linear, logistic, or Poisson regression models including the randomized treatment group as an independent variable, will be used to estimate the treatment effect between treatment groups. Normality will again be checked using qq-plot and, if necessary, appropriate transformations of the dependent variable will be made.

For the comparison of readmission rates between the treatment groups, the date of discharge from the hospital after surgery will be chosen as the starting observational time point and a Poisson model, considering readmissions collectively, will be fitted to estimate the incidence rates of readmission per treatment group within 90 days after discharge. The result will be reported as a rate ratio (RR) and the Poisson model will be corrected for overdispersion if necessary.

To estimate the hazard ratio for the first readmission, again with starting time point at discharge, a Cox-model will be used.

The Fagerström test results, the quality of life (SF-36 Index) and the smoking status (cigarettes smoked per days) will be measured repeatedly over time from baseline, and for each outcome, mixed-effects models will be used to estimate the treatment effect and also to quantify the time*treatment interaction. The result of NicAlert Saliva test between treatment groups will be evaluated by applying chi-square test.

Cost-effectiveness analyses will be performed from a health care institution as well as a population public health perspective. First, hospital costs in both arms with and without costs of the tobacco treatment specialist (TTS) consultation per session, and nicotine replacement products will be compared as averages per patient across treatment groups. Second, the incremental cost per additional quit and incremental cost per additional life year saved of the preoperative institutional smoking cessation program compared to usual care will be calculated. Utilities will be calculated based on quality-of-life measurements using the SF-36 questionnaire.

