### Outcomes {12}

The primary endpoint is the (CCI®) [9] within 90 days of surgery. The CCI is calculated as the sum of all Clavien–Dindo complications [17] (Additional file 1) that are weighted for their severity (multiplication of the median preference values from patients and physicians). The final formula yields a continuous scale that ranks the cumulative burden from any combination of complications from 0 to 100 in a single patient. As a composite complication score, the CCI has the advantage of reflecting the overall burden of the postoperative course that affects the health of patients and their quality of life. In addition, the CCI is a powerful endpoint in trials, as it allows sample size up to nine times lower compared with traditional morbidity endpoints [18]. Complications will be assessed from medical health records by an advanced nurse practitioner supported by a surgical resident and consultant, all of whom were already trained in the Clavien–Dindo classification in a pilot study. Outpatient information of complications treated at other institutions will be included.

Secondary endpoints are length and costs of hospital stay, readmission rates for inpatient hospital stay, smoking abstinence or nicotine reduction, nicotine dependence, mental health, quality of life, unplanned postoperative intermediate care or intensive care unit admissions and cost and. Secondary endpoints will be recorded up to a 12-month postoperative follow-up period and will be compared between the intervention and control group. Smoking abstinence or nicotine reduction will be assessed by measuring smoking status (cigarettes smoked per day) and nicotine dependence will be assessed using the Fagerström test [19]. Nicotine abstinence will be additionally confirmed by using the NicAlert cotinine saliva test. Quality of life will be assessed with the German version of the 36-Item Short Form Survey (SF-36; index values range from 0 to 1, with higher scores indicating better quality of life) including covering physical functioning, bodily pain, role limitations due to physical health problems, role limitations due to personal or emotional problems, emotional well-being, social functioning, energy/fatigue, and general health perceptions during the past 4 weeks [20]. Mental health will be assessed using the Hospital anxiety and depression scale (HADS) [21].

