Morbidity may influence the endpoints, therefore Charlson Comorbidity Index [22] and the American Society of Anaesthesiologists (ASA) physical status classification [23] will be assessed for each patient at baseline. The following characteristics measured at baseline are further described: age, gender, surgical procedure, underlying medical conditions and the stage of the Transtheoretical Model (TTM) of behaviour change.

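### Charlson index and ASA class are collected because morbidity may affect the endpoints, but the primary CCI model omits them: a modest loss of precision, not an error

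*Protocol article*

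**What the plan says.** Under Statistical methods for primary and secondary outcomes {20a}, the protocol article sets out the primary model: "Primary outcome CCI will be addressed with a multiple linear model, including a randomized treatment group, and the minimization variables". It names these variables as age up to 60 or over 60 and intermediate or high-risk surgery. When the section then speaks of adjustment for confounders, it means these two.

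Under Outcomes {12}, it gives the reason for two further baseline measurements: "Morbidity may influence the endpoints, therefore Charlson Comorbidity Index [22] and the American Society of Anaesthesiologists (ASA) physical status classification [23] will be assessed". They are taken on every patient. Age and surgical procedure are also recorded.

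Sequence generation {16a} uses the same two dichotomies for minimisation and justifies them as complication risk factors found in the institution's own retrospective cohort. The article gives no reason for leaving Charlson and ASA out of the primary model, or for using age only as a binary term.

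**The concern.** The protocol itself identifies comorbidity as something that may affect outcome and measures it for that reason. It then uses that information neither in the allocation nor in the primary model. Two things are at stake.

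- **Precision.** A baseline variable that predicts the CCI, if included in the linear model, reduces the residual variance and narrows the interval for the treatment difference. The data are already being collected.
- **Chance imbalance.** If one arm turns out to have more comorbidity, the imbalance feeds into the primary estimate except where it is correlated with age group and procedure risk. If the adjusted primary model was not settled beforehand, a later switch to it would look data-driven. This matters more here because Frequency and plans for auditing trial conduct {23} schedules unblinded safety analyses of the CCI after 50 and 100 patients.

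A smaller point is that a single cut at 60 discards part of what exact age could explain.

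**Working it through.** **Inputs from Sample size {14} and Sequence generation {16a}.** Mean CCI: the control value "was 13 and we therefore assume a CCI of 5.5 in the intervention group", so the difference is 13 − 5.5 = 7.5. SD: "The assumed standard deviation for the sample size calculation was 20". Target: "With anticipated 80% power, a two-sided significance level α of 5%, a sample size of 226 patients is planned". Enrolment: "With an additional 10% dropout, our aim is to enrol 251 patients". Allocation is 1:1, so 113 per arm.

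**Step 1: the plan's own figure.** The normal approximation gives n per arm = 2 × (1.960 + 0.842)² × 20² / 7.5² = 111.6, so 112 per arm and 224 in total. The two-sample t-test version gives 112.6, so 113 per arm and 226 in total, as stated. Dropout: 226 / 0.90 = 251.1, stated as 251. Power at 113 per arm from the noncentral t distribution is 80.1%. The sample size reproduces and is not in dispute.

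**Step 2: standard error under the plan.** SE = 20 × √(2/113) = 2.66 CCI points, so the 95% interval has a half-width of about 1.96 × 2.66 = 5.22.

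**Step 3: effect of extra covariates.** Let R² be the share of CCI variance explained beyond the present covariates. The documents do not give it, so a range is assumed. SD 20 is treated as the SD under the present model. The variance is multiplied by (1 − R²) and, for estimating k extra terms, by about 221/(221 − k). Here 221 is one less than the 222 residual degrees of freedom of the present four-parameter model (226 − 4). Charlson, continuous age and a three-category ASA term give k = 4 and a factor of 221/217 = 1.018.

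| Assumed extra R² | Power, no charge for terms | Power, k = 4 | SE, k = 4 |
|---|---|---|---|
| none (plan) | 80.1% | – | 2.66 |
| 2% | 80.9% | 80.2% | 2.66 |
| 5% | 82.1% | 81.4% | 2.62 |
| 10% | 84.1% | 83.4% | 2.55 |
| 15% | 86.1% | 85.5% | 2.48 |

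For example, at 10%: SE = 2.66 × √(0.90 × 1.018) = 2.55. Four terms break even at about R² = 4/221 = 1.8%.

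**Step 4: adding department as well.** With about nine extra terms the factor is 221/212 = 1.042. Power is 79.3% at R² 2% and 80.5% at 5%. Department could add explained variance of its own, but nothing in the document indicates how much.

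**Step 5: chance imbalance.** An omitted covariate with a given R² adds a random shift to the CCI difference with SD 20 × √R² × √(2/113). This is 0.59, 0.84 or 1.03 points at R² 5%, 10% or 15%, against a target of 7.5. As an illustration, take a comorbidity class holding half the patients. The SD of the between-arm difference in its share is √(2 × 0.25/113) = 6.65 percentage points. If that class has a mean CCI 10 points higher (assumed), a 2-SD imbalance moves the estimate by 2 × 0.0665 × 10 = 1.33 points, half of one standard error. These figures give no credit for correlation with the two minimised factors, so they lie towards the upper end.

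**Step 6: cutting age.** For a roughly normal age with a linear effect on the CCI (both assumed), a cut at the median keeps 2/π = 64% of the variance that continuous age explains, and a 30/70 split keeps 58%.

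Steps 3 and 4 use normal theory. The CCI may be skewed, so the powers are approximate.

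**The case against.** The planned model is a legitimate choice. It is prespecified, matches the allocation scheme, and has an empirical reason behind both factors. Outcomes {12} says that Charlson and ASA will be assessed; it does not promise adjustment. A reader might infer that the protocol contradicts itself or that the primary estimate is biased. Neither follows: the comparison is unbiased over randomisation, and the confidence interval already allows for chance imbalance.

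The gain rests wholly on an assumed R², and at 2% it vanishes once the extra terms are paid for. It would also be too strong to say that the trial has no margin. The article does not state whether SD 20 is a raw or a residual SD; if raw, the two planned covariates already give some margin. Interim analyses {21b} also provides a blinded re-check of the SD, with a possible increase in sample size.

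The statistical analysis plan (Additional file 3) is not shown and may contain a comorbidity-adjusted sensitivity analysis, so one cannot say that any such adjustment would be post hoc.

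All of this stands, and it limits the point to efficiency and prespecification. It does not remove the point. Section {20a} names the covariates of the primary model, and a sensitivity analysis elsewhere would leave that list unchanged.

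**Conclusion.** The point holds as a cheap improvement. The protocol gives its own reason to think comorbidity prognostic, measures it on everyone, and leaves it out of both minimisation and the primary model. For an assumed extra R² of 5% to 15% and about four added terms, the net gain is roughly 1 to 5 percentage points of power (81.4% to 85.5%, against 80.1%), with the standard error falling from 2.66 to between 2.62 and 2.48. At 2% or below there is essentially nothing to gain. The added value is a primary model that answers a foreseeable dispute over comorbidity imbalance in advance.

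The omission, collection of the two measures and reproduction of the sample size are certain from the text; the size of the gain is not. A reader might conclude that the trial is underpowered or its primary analysis invalid because of this omission. The document does not support that: the stated 226 and 251 reproduce, and the model contains both minimisation factors.

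**What to change.** In {20a}, and correspondingly in the analysis plan, keep treatment group and both minimisation factors (age group and procedure risk) in the primary model. Add Charlson index, ASA class as an ordinal or few-category term, and age as a continuous term. Fix the exact coding in advance.

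Settle this before any by-arm look at the CCI, including the unblinded safety analyses after 50 and 100 patients. Report the present two-factor model as a sensitivity analysis. Leave the sample size unchanged, since R² is unknown. Do not add department: it costs about five further terms with no documented gain.

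The cost is three or four degrees of freedom out of 222, a variance charge of about 1.8% for four terms (221/217), and a change of wording. No new data are needed.

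### The secondary models name only the randomised arm, although allocation is minimised on two factors that the plan regards as prognostic for complications

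*Protocol article*

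**What the plan says.** All points are in the protocol article.

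- **Allocation (Sequence generation {16a}).** Assignment is 1:1 by minimisation on two factors: "Before randomisation patients will be pre-stratified for age (≤60, >60 years) and procedure (intermediate versus high-risk procedures". Their prognostic role is stated: "Both factors have been identified in a previous retrospective cohort study at our institution as risk factors for complications".
- **Primary model (Statistical methods {20a}).** "Primary outcome CCI will be addressed with a multiple linear model, including a randomized treatment group, and the minimization variables".
- **Secondary models (same paragraph of {20a}).** "For the secondary outcomes, linear, logistic, or Poisson regression models including the randomized treatment group as an independent variable, will be used". No other covariate is named. The Poisson and Cox readmission models, the mixed models and the chi-square test described after it do not mention the minimisation factors either.
- **Baseline comorbidity (Outcomes {12}).** "Morbidity may influence the endpoints, therefore Charlson Comorbidity Index [22] and the American Society of Anaesthesiologists (ASA) physical status classification [23] will be assessed". No analysis described in the article then uses either score.

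Section {20a} also refers to a detailed SAP (Additional file 3), which was not available for this review.

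**The concern.** Minimisation forces the arms to be alike on its factors. If those factors predict the outcome, the difference between arms varies less from trial to trial than it would under simple randomisation. A linear model with the arm alone does not know this. It leaves the variation due to the factors in the residual, so it reports a standard error larger than the true one. Intervals then cover more than 95% of the time, tests reject less than 5% of the time under the null, and power is lost.

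The plan avoids this for the CCI but, as written, not for the secondary outcomes. The outcomes at stake are those tied to complications, because that is where the article documents the factors as prognostic.

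A second, separate matter is efficiency in the primary analysis. Two comorbidity scores are collected because they may bear on the endpoints, yet the article makes no use of them in the CCI model.

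**Working it through.** **Inputs from the article (Sample size {14}).** Control mean CCI 13, intervention mean 5.5, difference 7.5, SD 20, two-sided 5%, power 80%, 226 patients, 10% dropout, 251 enrolled.

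**Assumption.** The share of variance explained, R², is not given anywhere. It is set at 5, 10 and 20%.

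**1. The plan's own figures.** The normal approximation gives n per arm = 2 × (1.960 + 0.842)² × 20² / 7.5² = 111.6, so 112 per arm and 224 in total. The two-sample t-test gives 112.6, so 113 per arm and 226 in total, as stated. Dropout: 226 / 0.90 = 251.1, against 251 stated. The figures reproduce without any covariate.

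**2. Linear model without the minimisation factors.** With near-perfect balance the true standard error is √(1 − R²) times the one the model reports. Hence:

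- excess interval width = 1/√(1 − R²) − 1
- true size = 2 × [1 − Φ(1.960/√(1 − R²))]

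For power, take a secondary outcome with the same standardised difference as the primary (7.5/20) and 113 per arm. This is a further assumption, since the article powers no secondary outcome. The signal ratio is 7.5 / (20 × √(2/113)) = 2.819. Then:

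- unadjusted power = Φ((2.819 − 1.960)/√(1 − R²))
- adjusted power = Φ(2.819/√(1 − R²) − 1.960)

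| R² of the two factors | Excess width | True size | Coverage | Power, arm only | Power, adjusted | Loss (points) |
|---|---|---|---|---|---|---|
| 5% | 2.6% | 4.4% | 95.6% | 81.1% | 82.4% | 1.3 |
| 10% | 5.4% | 3.9% | 96.1% | 81.7% | 84.4% | 2.7 |
| 20% | 11.8% | 2.8% | 97.2% | 83.2% | 88.3% | 5.1 |

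**3. Check by simulation.** Settings, all assumed: 226 patients, two factors each split 50/50, minimisation with a biased coin of 0.8, 3,000 runs. For R² of 5, 10 and 20%:

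- size was 4.8, 3.5 and 2.7% with the factors omitted, and 5.7, 4.8 and 4.7% with them included (Monte Carlo error about 0.4 points);
- power was 80.7, 81.4 and 81.9% with the factors omitted, and 82.0, 84.1 and 87.7% with them included.

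The direction and rough size agree with the formulas.

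**4. Models that are not linear.** The figures in step 2 do not carry over to logistic or Cox models. Leaving out prognostic factors costs power there too, but adjustment changes the estimand to a conditional odds or hazard ratio, so it does not simply narrow the interval. The figures were not derived for the Poisson model either.

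**5. Charlson and ASA in the primary model.** Residual SD = 20 × √(1 − R²), with R² now the extra share explained by the two scores.

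| Extra R² | Residual SD | Power at 226 | Total for 80% power |
|---|---|---|---|
| 0% | 20.0 | 80.5% | 224 |
| 5% | 19.5 | 82.4% | 214 |
| 10% | 19.0 | 84.4% | 202 |
| 20% | 17.9 | 88.3% | 180 |

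This starts from the full SD of 20, as if the minimisation factors already in the model explained nothing. If they explain some of the variance, planned power is already above 80% and the scores add to that.

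**The case against.** **Including the arm does not mean the arm only, and the SAP may list covariates.** This is the strongest reply, and a condensed article may leave detail to its SAP. But the point concerns a method that the article does state. The sentence on secondary models comes shortly after one that spells out the covariates of the primary model, and it names the arm alone. Treatment-only is the natural reading, and the text should be corrected or aligned even if the SAP says otherwise.

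**The prognostic claim is limited to complications.** This stands. The article gives no evidence that age or procedure risk predicts smoking, nicotine dependence or cotinine results, so no loss can be claimed for those.

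**The size is assumed and the error is conservative.** This also stands. No R² is given, at 5% or below the loss is small, and there is no added risk of a false positive.

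**Charlson and ASA are a matter of preference.** Largely right. They are not allocation factors, the article says only that morbidity may matter, and it makes no promise to adjust for them. Leaving them out breaks nothing.

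Two stronger readings are tempting and not supported:

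- A reader might infer that the primary intervals are also too wide or that the trial is underpowered. The primary model contains both minimisation factors, so its coverage is as intended, and 226 patients give the planned power with no covariates at all.
- A reader might infer that the mixed models for cigarettes per day, Fagerström score and SF-36 treat the baseline value as a response, which would dilute the effect. The article says only that these outcomes "will be measured repeatedly over time from baseline". That tells when measurement begins, not how the baseline value enters the model, and the same sentence plans a time-by-treatment interaction.

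**Conclusion.** The point holds for the secondary models. The plan balances allocation on two factors it considers prognostic for complications, adjusts for them in the primary analysis, and then specifies the secondary models with the arm alone. For complication-related outcomes analysed by linear models, tests and intervals are conservative: true size about 4.4, 3.9 or 2.8%, and about 1, 3 or 5 power points lost, if the factors explain 5, 10 or 20% of the variance. These figures rest on the assumed R², on near-perfect balance and, for power, on the primary outcome's standardised difference. For logistic and Cox models only the loss of power can be asserted.

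Using Charlson and ASA in the primary model would be a gain in efficiency, not the repair of an error. It would bring power from about 80% to 82, 84 or 88% for an assumed extra 5, 10 or 20% of variance explained.

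**What to change.** 1. **Secondary outcomes.** State that the secondary regression models, including the Poisson and Cox readmission models, contain the arm and both minimisation factors, coded as in the primary model. For logistic and Cox models, state that the reported effect is conditional on these factors. If the SAP already says this, bring the protocol wording into line with it.
2. **Primary outcome (optional, for efficiency).** Prespecify, before unblinding, the Charlson index and ASA class as covariates in the CCI model. If the sponsor prefers to leave the primary model as it is, put them in a named sensitivity model or say that they are descriptive only.

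The cost is a change of wording and a few degrees of freedom. All the variables are already collected, and the sample size need not change.
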